# SYNOPSIS

|                                                    |                                                                                                                                                                                                                                                                                                         |
|----------------------------------------------------|---------------------------------------------------------------------------------------------------------------------------------------------------------------------------------------------------------------------------------------------------------------------------------------------------------|
| Title                                       | Enhancing Trauma Resuscitation Simulation Training with the Use of Virtual Reality (The Trauma SimVR Study)                                                                                                                                                                                             |
| Protocol date                               | March 22 nd , 2024                                                                                                                                                                                                                                                                           |
| Protocol version                            | 1.4                                                                                                                                                                                                                                                                                                     |
| Ethics committee number                     | 1388/2023                                                                                                                                                                                                                                                                                               |
| ClinicalTrials.gov identifier (NCT number): | NCT06445764                                                                                                                                                                                                                                                                                             |
| Hypothesis                                  | We hypothesize that the use of VR simulation in the context of trauma CPR training will lead to improved performance in the management of trauma patients going into cardiac arrest, with greater confidence in clinical decision-making, resulting in shorter times to order/perform critical actions. |
| Primary aim                                 | The primary aim of this study is to evaluate the effectiveness of using VR technology, as opposed to e-learning preparation, to equip learners with the skills and knowledge necessary for in-person simulation training and to improve their performance in TCA management skills.                     |
| Secondary aim                               | The secondary aims are to assess gender differences in performance, the frequency of protocol deviations, the cognitive load, and the gaze behavior between groups as well as participants' acceptance and impressions of VR in medical education.                                                      |
| Design                                      | Single-center, prospective, single-blind, randomized, controlled trial                                                                                                                                                                                                                                  |
| Intervention                                | VR simulation training for managing trauma patients going into cardiac arrest                                                                                                                                                                                                                           |
| Control                                     | Training/preparation for the management of trauma patients going into cardiac arrest using an e-learning course                                                                                                                                                                                         |
| Sample size                                 | 67                                                                                                                                                                                                                                                                                                      |
| Inclusion criteria                          | Junior physician (common-trunk) or first-year resident in the field of anesthesiology, intensive care, emergency medicine or traumatology at the Medical University of Vienna; only people who do not need eyeglasses for using VR; ≥ 18 years                                                          |
| Exclusion criteria                          | Pre-disposition for cybersickness (motion sickness, pregnancy, pre-existing cybersickness)                                                                                                                                                                                                              |
| Drop-out criteria                           | Use of any other theoretical or hands-on trauma and/or CPR training opportunities outside those given in the respective randomized group during study participation; incomplete preparation with the assigned study method                                                                              |

*CPR = cardiopulmonary resuscitation; VR = virtual reality*

## LIST OF ABBREVIATIONS

| Abbreviation | Definition                                             |
|---------------------|---------------------------------------------------------------|
| ACLS                | Advanced cardiac life support                                 |
| AE                  | Adverse event                                                 |
| AHA                 | American Heart Association                                    |
| ALS                 | Advanced life support                                         |
| AOI                 | Area of interest                                              |
| ATLS                | Advanced trauma life support                                  |
| BLS                 | Basic life support                                            |
| CASTesting          | Cardiac arrest simulation testing                             |
| CPR                 | Cardiopulmonary resuscitation                                 |
| CRM                 | Crew resource management                                      |
| ERC                 | European Resuscitation Council                                |
| eFAST               | Extended Focused Assessment with Sonography for Trauma        |
| etCO 2   | End-tidal carbon dioxide                                      |
| HCP                 | Healthcare providers                                          |
| ID                  | Identification                                                |
| IHCA                | In-hospital cardiac arrest                                    |
| ILCOR               | International Liaison Committee of Resuscitation              |
| MedUni Vienna       | Medical University of Vienna                                  |
| NASA-TLX            | National Aeronautics and Space Administration Task Load Index |
| PEA                 | Pulseless electric activity                                   |
| POCUS               | Point-of-care ultrasound                                      |
| ROSC                | Return of spontaneous circulation                             |
| spO 2    | Oxygen saturation                                             |
| SUS                 | System usability scale                                        |
| TCA                 | Traumatic cardiac arrest                                      |
| VR                  | Virtual reality                                               |

# 1 BACKGROUND

Traumatic cardiac arrest (TCA) is an incredibly devastating condition with a low survival rate (1) that requires urgent recognition, rapid intervention, and specialized resuscitation skills in both in-hospital and out-of-hospital settings. In Austria, as in many other countries, the transfer of prehospital trauma patients to specialized emergency departments, so-called shock rooms, staffed by anesthesiologists and traumatologists is critical because they require highly specialized interventions such as bleeding control, airway management, patient blood management, etc. and patients are often at risk of cardiac arrest upon arrival. However, in-hospital cardiac arrest (IHCA) care has been shown to be often substandard and not fully consistent with international guidelines (2–5). Therefore, the International Liaison Committee of Resuscitation (ILCOR) and the American Heart Association (AHA) recommend focused cardiopulmonary resuscitation (CPR) training for IHCA as a primary area of interest to improve survival from IHCA (6,7).

Simulation is the gold standard for training various medical scenarios in a safe and forgiving environment (8–10), with an additional focus on patient safety (9,11). This is particularly important in the context of rare but life-threatening conditions (8,11,12) such as TCA. In contrast, it is important to note that the highly specialized skills required to manage TCA may not be commonly taught in standard adult advanced life support (ALS) courses and simulations. In addition, the procedures required for TCA management deviate to some extent from standard ALS care, as suggested by the European Resuscitation Council (ERC) and are rarely used in daily practice. As a result, healthcare providers (HCPs) need to undergo rigorous training (13–15) to ensure that they have the necessary skills and expertise to effectively manage TCA patients when needed. Although simulation-based training is an effective way to improve trauma resuscitation skills, the complexity of TCA scenarios and the need for specialized equipment and trained personnel often limit simulation opportunities and make them very expensive and rare. This could lead to poor training outcomes and reduced patient survival rates.

To address this issue, innovative, less expensive, and more accessible training methods need to be developed. Virtual reality (VR) simulation is an emerging approach that enables realistic and immersive training scenarios without the need for expensive equipment or physical space (11,16–18). In-situ simulation, on the other hand, allows for training in the actual clinical environment, allowing for the assessment of team dynamics and human factors that may affect resuscitation outcomes. The combination of pre-course VR preparation (15,19) and in-situ simulation approaches (15,19–21) could ultimately improve the TCA management skills of HCPs and also have a positive impact on the outcomes of critically injured patients. Blended learning approaches appear to provide the best educational value for CPR training (15,20,22–24).

Therefore, the primary aim of this study is to evaluate the effectiveness of using VR technology, as opposed to e-learning (19,25–27) preparation, to equip learners with the skills and knowledge necessary for in-person simulation training and to improve their performance in TCA management skills. The secondary aims are to assess gender differences in performance (28,29), the frequency of protocol deviations, the cognitive load, and the gaze behavior between groups as well as participants' acceptance and impressions of VR in medical education.

## 2 RESEARCH HYPOTHESIS AND OBJECTIVES

### 2.1 Hypothesis

We hypothesize that the use of VR simulation in the context of trauma CPR training will lead to improved performance in the management of trauma patients going into cardiac arrest, with greater confidence in clinical decision-making, resulting in shorter times to order/perform critical actions.

### 2.2 Primary Objective

The primary objective of this study is to evaluate whether a VR-based approach is superior to an e-learning-based approach in the context of trauma CPR training and preparation prior to testing trainee performance in an in-person simulation session. The primary outcome measure is the time from the start of chest compressions to critical action #3 (*mini-thoracotomy*; Table 1) in the simulation (assessment) session.

### 2.3 Secondary Objectives

- 1) Comparing the number of participants who did not recognize and treat the underlying condition (one or more missed critical actions) of the TCA between randomized groups.
- 2) Comparing the number of participants who prematurely declared a patient dead (before the 15-minute time limit of the scenario).
- 3) Comparing the time to critical actions, excluding the primary outcome measure, between randomized groups.
- 4) Comparing the proportions of the respective protocol deviations between randomized groups.
- 5) Evaluate gender differences in the primary outcome.
- 6) Comparison of cognitive load between the randomized groups while performing the simulated assessment scenarios as measured by the National Aeronautics and Space Administration Task Load Index (NASA TLX).
- 7) Eye-tracking
  - a) Comparing the gaze behavior (dwell-time in AOIs, fixation count, and average fixation duration) between randomized groups.
  - b) Comparing the relative time when no AOI is illustrated between randomized groups.
- 8) Using a 5-point Likert scale:
  - a) Participants' subjective impressions of their learning progress when using VR/e-learning.

- b) Participants' subjective impressions of their level of frustration when using VR/e-learning.
  - c) Participants' subjective impression of their level of enjoyment when using VR/e-learning.
  - d) Participants' subjective confidence in recognizing and providing initial care to polytraumatized patients in cardiac arrest in the simulation sessions.
  - e) Participants' subjective overall performance in the simulation sessions.
  - f) Participants' overall performance in the simulation sessions from the expert's point of view.
- 9) To assess the correlation between how often participants have played VR and non-VR video games in the past 12 months and between the ages of 6 and 18 and the primary outcome?
- 10) The incidence rate of VR-related adverse events (AEs).
- 11) System usability scale (SUS) for the use of the VR simulations.

## 3 Methodology

### 3.1 Study population

The focus of this study is on junior physicians in the so-called common-trunk phase, who have already completed their medical studies and are working as physicians but are not yet enrolled in a definitive residency program, as well as first-year residents in anesthesiology/intensive care, emergency medicine, and traumatology at the Medical University of Vienna (MedUni Vienna).

Participants will be recruited through bulletin board postings (Additional file #5), email lists, and social media channels of MedUni Vienna.

#### 3.1.1 Inclusion Criteria

To be eligible for this study, participants must meet all of the following inclusion criteria:

- Junior physician (common-trunk) or first-year resident in the field of anesthesiology, intensive care, emergency medicine, or traumatology at MedUni Vienna
- Only people who do not need eyeglasses for using VR
- $\geq 18$  years

#### 3.1.2 Exclusion criteria

Participants meeting the following criteria will not be included in the study:

- Pre-disposition for cybersickness (motion sickness, pregnancy, pre-existing cybersickness)

#### 3.1.3 Drop out criteria

Participants will be withdrawn from the study if any of the following criteria are met:

- Use of any other theoretical or hands-on trauma and/or CPR training opportunities outside those given in the respective randomized group during study participation
- Incomplete preparation with the assigned study method

## 3.2 Study design

This study is a single-center, prospective, single-blind, randomized, controlled trial. It aims to assess the efficacy of VR as a more effective preparation method for in-person simulation trainings, compared to e-learning. The focus is on improving physicians' trauma CPR management skills.

All recruited participants will watch a 60-minute video to learn about the requirements, steps, and other important information about this study. Furthermore, this introductory video will give an overview of management strategies for trauma patients going into cardiac arrest in an in-hospital setting and provides links to the guidelines (30–32) on which this study is based. It also indicates that knowledge of the content of the guidelines is a prerequisite for Phases 2 through 3. This video can be viewed as often as desired throughout the study. Participants will also be required to complete the electronic Questionnaire 1 (Additional file #2) prior to randomization, which assesses participants' baseline characteristics (including the German versions of the "Openness to Experience" subscale of the 100-item HEXACO-PI-R test (33,34) and the Technology Readiness Scale (35)).

Each participant will then complete either the e-learning course (control group) or the VR training simulations (intervention group) over a two-week period, both focusing on the same content. Both groups will spend approximately the same amount of time learning the same content, which will prepare the participants for the assessment in the simulation session. If participants do not complete the entire e-learning course or all four VR simulations, they will be dropped from the study.

After Phase 2, all participants will attend the simulation session and will be evaluated in the role of medical team leader of a standardized TCA scenario (Phase 3).

In addition, each participant will be required to complete Questionnaire 2 (Additional file #3) immediately following the simulation session in Phase 3. Only the intervention group will be required to complete the VR system usability portion of this questionnaire. The system usability scale (SUS) (36,37) will be translated and used in German.

[figure not shown]

**Figure 1.** The course of events during the study.

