### 3.2.1 Randomization

Recruited participants will be randomly assigned to the control or intervention group on an equal basis by gender. Participants will not know their allocation to either group until they have watched the entire introductory video and completed Questionnaire 1. Randomization will be performed using the web-based randomization software Randomizer from MedUni Vienna (38).

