### 3.3 Sample size

A sample size of 30 in each group will have 80% power to detect a probability of at least 0.71 that an observation in Group 1 is less with respect to the primary outcome variable than an observation in Group 2 using a Wilcoxon (Mann-Whitney) rank-sum test with a 0.05 two-sided significance level.

Based on an expected drop-out rate of 10%, 67 participants will be recruited to participate in this study.

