### **Primary objective/outcome:**

A two-sided generalized Wilcoxon test with a 5% significance level will be used to compare the primary outcome between the randomized groups. Participants who do not identify and treat the underlying condition of TCA will be censored at 15 minutes. Furthermore, if patients are declared dead prematurely, the observation will also be censored at 15 minutes.

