### **Secondary objectives/outcomes:**

A two-sided generalized Wilcoxon test will also be used to compare times to critical actions, excluding the primary outcome. The number of participants who did not recognize and treat the underlying condition of the TCA, and the number of participants declaring the patient dead prematurely, will be compared between groups calculating the chi-square test. Protocol deviations will be analyzed separately for each protocol deviation listed in Table 2. The respective frequencies of each protocol deviation will also be compared between groups calculating the chi-square test. Fisher's exact test will be used if one or more expected cell frequencies are less than 5.

In addition, the Wilcoxon rank sum test will also be used to compare the gaze behavior (dwell-time in AOIs, fixation count and average fixation duration, and relative time when no AOI is illustrated) and the NASA-TLX scores (global and per objective) between randomized groups.

Furthermore, a multivariable Cox regression model (including an interaction term) will be used to determine the influence of gender on the primary outcome, and the potential modifying effect of gender on the training effect (= group effect). The HEXACO subscale and the Technology Readiness Score will also be included in the multivariable model to adjust for potential imbalances between the randomized groups.

The following Spearman correlation coefficients will be calculated corresponding to the remaining secondary objectives:

- Correlation of 5-point Likert scales between the frequency of playing classic video games and the primary outcome

5-point Likert scales, the incidence rate of VR-related AEs, and the SUS scores will be reported using descriptive statistics only.

Observations with missing data in the primary outcome measure will be excluded from statistical analyses. Boxplots will be used to illustrate calculations. A two-sided p-value of  $< 0,05$  will be considered statistically significant.

Due to the singular primary objective, no correction for multiple testing will be made. All secondary objectives are exploratory in nature and will be used to generate further hypotheses.

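### Dropping randomised participants for incomplete preparation or outside training makes the primary comparison completers-only and open to bias in either direction

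*Protocol*

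**What the plan says.** Three places in the protocol fix the rule on incomplete preparation. Section 3.1.3 lists it as a ground for withdrawal. Section 3.2 says "If participants do not complete the entire e-learning course or all four VR simulations, they will be dropped from the study". Section 3.2.2 repeats this and makes completion a condition for entering Phase 3, where the primary outcome is measured.

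The second ground for withdrawal in section 3.1.3 is "Use of any other theoretical or hands-on trauma and/or CPR training opportunities outside those given in the respective randomized group during study participation". Table 3 takes this item from Questionnaire 2, which section 3.2 places immediately after the assessed simulation.

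Both grounds arise after randomisation. Section 3.2.1 lets participants learn their arm once they have watched the introductory video and completed Questionnaire 1, so they know it while they prepare.

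On the analysis, section 3.5 says "A two-sided generalized Wilcoxon test with a 5% significance level will be used to compare the primary outcome between the randomized groups" and "Observations with missing data in the primary outcome measure will be excluded from statistical analyses". It describes no analysis that brings withdrawn participants back. The objective in section 2.2 is superiority of the VR-based approach.

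**The concern.** Randomisation makes the two groups comparable at allocation. Any rule that then removes people for what they did under their allocated method can undo this. A participant who does not finish is never assessed, so the time to mini-thoracotomy does not exist for that person and no later analysis plan can recover it. A participant who reports outside training has already been through the scenario, and is withdrawn although the recording exists.

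The reasons for not finishing need not be the same in the two arms. The protocol names some that only the VR arm can have: cybersickness and related symptoms (VR-related adverse events, section 3.2.2) and technical difficulties with the headset (section 3.6.1). If the people lost from one arm would have been slower than those who stay, that arm looks faster with no training effect at all. Whether learners get through a method is also part of how well it works as preparation, which is what section 2.2 asks.

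**Working it through.** **Inputs from the protocol**

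- Test and level: two-sided 5% (section 3.5).
- Size: "A sample size of 30 in each group will have 80% power to detect a probability of at least 0.71", "using a Wilcoxon (Mann-Whitney) rank-sum test with a 0.05 two-sided significance level" (section 3.3).
- Recruitment: "Based on an expected drop-out rate of 10%, 67 participants will be recruited to participate in this study" (section 3.3).
- Allocation: "randomly assigned to the control or intervention group on an equal basis by gender" (section 3.2.1), taken here as 34 VR and 33 e-learning.

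**Inputs assumed, because the protocol gives none:** how losses split between the arms, and how strongly dropping relates to slow performance. Both are varied below. The total is held at 10% of 67 = 6.7, about 7 people.

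**The plan's own figure.** Noether's formula for the rank-sum test gives total N = (1.960 + 0.842)² / (12 × 0.25 × (0.71 − 0.5)²) = 7.849 / 0.1323 = 59.3, so 30 per group. Then 60 / 0.9 = 66.7, so 67. Both stated figures reproduce. The 10% allowance replaces numbers; it does not restore comparability.

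**Bias when there is no training effect.** In each of 40,000 simulated trials per setting, every participant has a normally distributed time and a latent dropping score correlated with it. The participants highest on that score are dropped from each arm, and the rest are compared with a rank-sum test. Censoring at 15 minutes is ignored. P is the probability that a VR participant is faster than an e-learning participant; it should be 0.500.

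| Losses VR / e-learning | Type I error, correlation 0 | Correlation 0.3 | Correlation 0.5 | P at 0.5 | Significant in favour of VR at 0.5 (nominal 2.5%) |
|---|---|---|---|---|---|
| 4 / 3 | 5.0% | 5.2% | 5.5% | 0.506 | 3.2% |
| 5 / 2 | 4.9% | 5.5% | 6.4% | 0.520 | 4.9% |
| 6 / 1 | 5.0% | 5.8% | 7.7% | 0.535 | 6.9% |
| 7 / 0 | 4.9% | 6.7% | 10.3% | 0.550 | 9.8% |
| 0 / 7 | 5.2% | 6.8% | 10.4% | 0.450 | 0.5% |

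Simulation error on a 5% rate is about √(0.05 × 0.95 / 40,000) = 0.1 percentage point.

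Material bias needs two things together: clearly unequal losses, and a link between dropping and performance. With no link, the error rate stays at about 5% whatever the split. Reversing the split reverses the direction.

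**Power if everyone is assessed and analysed by allocated group.** Power = Φ(√(3N) × (P − 0.5) − 1.960). With N = 67 and P = 0.71: √201 × 0.21 − 1.960 = 1.017, or 84.5%. If a share of the VR arm does not complete and gains nothing (an assumption), P is a weighted mean of 0.71 and 0.5:

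| VR non-completion | P | Power with 67 | Total N for 80% |
|---|---|---|---|
| 5% | 0.95 × 0.71 + 0.05 × 0.5 = 0.700 | 80.7% | 66 |
| 10% | 0.90 × 0.71 + 0.10 × 0.5 = 0.689 | 76.4% | 74 |
| 15% | 0.85 × 0.71 + 0.15 × 0.5 = 0.679 | 71.6% | 83 |

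**The case against.** **The rule is symmetric, and direction is not shown.** It applies to both methods, and no drop-out by arm is given. A reader might infer from the VR-only reasons for stopping that the rule favours VR. The documents do not support this. Section 3.1.2 excludes people predisposed to cybersickness before randomisation, section 3.2.2 adds an orientation module on the headset, and section 3.6.1 puts a team member on hand for technical problems. These measures reduce the VR-specific risk without removing it, and e-learning could lose more people for other reasons. This part of the objection stands.

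**The size may be small.** At the planned drop-out with nearly balanced losses, the error rate barely moves. A reader could also build an alarming figure: with all 7 losses in the VR arm and a correlation of 1.0, the simulated type I error is 28.4%. That requires dropping to be wholly determined by slow performance and to occur in one arm only. Nothing in the protocol points to it, and it should not be quoted as the expected size.

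**Withdrawal for outside training is not withdrawal on a known result.** A reader might infer that people can be removed once their result is seen. Section 3.2.4 has blinded experts, not involved in conduct, score the videos in Phase 4, and the criterion is a fixed yes/no item. What remains is narrower: the self-report that decides withdrawal is given by someone who has just been through the scenario. Its effect is not modelled above and its direction is unknown.

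**A completers' question may be intended.** Section 3.2 speaks of efficacy. But section 2.2 sets superiority of the approach as the objective, the Synopsis and section 1 speak of effectiveness, and comparing those who happen to finish is not a randomised comparison under either word.

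**An analysis plan could settle this.** It could for outside training, where the outcome exists. It could not for non-completers, who are never assessed; this is a rule of conduct fixed in the protocol.

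**Conclusion.** The point holds. By its stated rules the protocol makes the primary superiority comparison completers-only, and that comparison can be biased toward either method. Direction and size cannot be established from the document.

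With about 7 losses, no true effect and an assumed correlation of 0.5, two-sided type I error runs from 5.5% for nearly balanced losses to about 10% when all losses fall in one arm, in favour of whichever arm lost people. It stays at 5% if dropping is unrelated to performance. These figures rest on assumed splits and correlations, normally distributed times and no censoring. The Cox model in section 3.5, which adjusts for the HEXACO subscale and Technology Readiness, is a secondary analysis and does not protect the primary unadjusted test.

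**What to change.** Change sections 3.1.3, 3.2 and 3.2.2 so that participants with incomplete preparation or outside training stay in the study and are invited to the Phase 3 assessment unless they withdraw themselves (section 4.2). State in section 3.5 that the primary analysis includes all randomised participants with an assessment, by allocated group. Keep the two criteria only to define a secondary per-protocol analysis. Report losses by arm and reason.

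The cost is protocol wording and up to about 7 more assessments of people already recruited; some may still withdraw. Keeping users of outside training adds no assessment, because they have already had theirs. The effect may be diluted. Section 3.3 should state this beside its power: if 10% of the VR arm do not complete and gain nothing, P falls from 0.71 to about 0.69 and power with 67 is about 76%, against 84.5% without dilution. Holding 80% under that assumption would take 74 assessed participants, so the sponsor should decide openly whether to accept the lower power or recruit more.
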